## Abstract

**Background:**

*Streptococcus pneumoniae* is the bacterial agent which most frequently causes pneumonia. In some Scandinavian countries, this infection is treated with penicillin V since the resistances of pneumococci to this antibiotic are low. Four reasons justify the undertaking of this study; firstly, the cut-off points which determine whether a pneumococcus is susceptible or resistant to penicillin have changed in 2008 and according to some studies published recently the pneumococcal resistances to penicillin in Spain have fallen drastically, with only 0.9% of the strains being resistant to oral penicillin (minimum inhibitory concentration>2 μg/ml); secondly, there is no correlation between pneumococcal infection by a strain resistant to penicillin and therapeutic failure in pneumonia; thirdly, the use of narrow-spectrum antibiotics is urgently needed because of the dearth of new antimicrobials and the link observed between consumption of broad-spectrum antibiotics and emergence and spread of antibacterial resistance; and fourthly, no clinical study comparing amoxicillin and penicillin V in pneumonia in adults has been published. Our aim is to determine whether high-dose penicillin V is as effective as high-dose amoxicillin for the treatment of uncomplicated community-acquired pneumonia.

**Methods:**

We will perform a parallel group, randomised, double-blind, trial in primary healthcare centres in Spain. Patients aged 18 to 65 without significant associated comorbidity attending the physician with signs and symptoms of lower respiratory tract infection and radiological confirmation of the diagnosis of pneumonia will be randomly assigned to either penicillin V 1.6 million units thrice-daily during 10 days or amoxicillin 1,000 mg thrice-daily during 10 days. The main outcome will be clinical cure at 14 days, defined as absence of fever, resolution or improvement of cough, improvement of general wellbeing and resolution or reduction of crackles indicating that no other antimicrobial treatment will be necessary. Any clinical result other than the anterior will be considered as treatment failure. A total of 210 patients will be recruited to detect a non-inferiority margin of 15% between the two treatments with a minimum power of 80% considering an alpha error of 2.5% for a unilateral hypothesis and maximum possible losses of 15%.

**Discussion:**

This pragmatic trial addresses the long-standing hypothesis that the administration of high doses of a narrow-spectrum antibiotic (penicillin V) in patients with non-severe pneumonia attended in the community is not less effective than high doses of amoxicillin (treatment currently recommended) in patients under the age of 65 years.

**Trial registration:**

EudraCT number 2012-003511-63.

## Background

*Streptococcus pneumoniae* is the bacterial agent which most frequently causes respiratory tract infections. Indeed, it is the most common bacteria in acute sinusitis, acute otitis media and community-acquired pneumonia. In some European countries, mainly those located in Northern Europe, pneumonia is treated with penicillin V since the resistances of these pneumococci to this antibiotic are low [1]. In the last years a phenomenon of greater community prescription of broad-spectrum antibiotics has been taking place in many countries, with amoxicillin-clavulanate and amoxicillin being the antibiotics most frequently prescribed by family practitioners in Spain [2,3]. Antimicrobial resistance may be a cause of therapeutic failure. It is identified by measuring the minimum inhibitory concentration (MIC) of the antimicrobial agent able to inhibit the growth of the microorganism. The cut-off points are MICs which define the infections as susceptible (treatable), with intermediate resistance (possibly treatable with higher doses) and resistant (not treatable). After re-evaluation taking new clinical studies into account, in January 2008 the *Clinical and Laboratory Standards Institute* published new cut-offs for penicillin [4]. These new cut-off points were determined on the basis of a series of criteria: first, by the pharmacokinetic and pharmacodynamic properties of the antimicrobial agents and second, by the data published relating MICs to the clinical outcome of the patients with pneumococcal infections. With the previous criteria a pneumococcus was considered to be susceptible with an MIC<0.06 μg/ml, to have intermediate resistance at between 0.12 and 2 μg/ml and to be resistant when the MIC was >2 μg/ml. At present, the new cut-off points for patients with meningitis receiving endovenous penicillin are <2, 4 and >8 μg/ml, respectively, unifying penicillin and amoxicillin. According to the results of the SAUCE 4 study published in 2010, the pneumococcal resistances to penicillin in Spain have fallen drastically, with only 0.9% of the strains being resistant to oral penicillin (MIC>2 μg/ml) [5]. In view of these results pneumonia could be treated with penicillin in Spain. In US the American Society of Infectious Diseases also recommends that patients with pneumonia be treated with penicillin if the causative strain of the infection is susceptible to this antibiotic [6].

### Study justification

Four reasons justify the undertaking of this study and these are: a) as mentioned above the cut-off points which determine whether a pneumococcus is susceptible or resistant to penicillin have changed; b) there is no correlation between pneumococcal infection by a strain resistant to penicillin and therapeutic failure in pneumonia. Treatment failure has been described in pneumonias treated with macrolides and fluoroquinolones. Curiously however, in contrast with the latter, in a review of clinical failures due to antimicrobial resistance no cases of therapeutic failure were reported with β-lactams prescribed at adequate doses [7]. It is important to know that a large proportion of patients die because of the severity of their disease and the associated comorbidity but not due to failure of the antibiotic. Thus, the study by Pallarés *et al.* has provided evidence that the risk of death by pneumococcal pneumonia treated with bencilpenicillin or ampicillin was similar regardless of whether the patients were infected with germs resistant or not to penicillin [8]. In other studies evaluating the effectiveness of penicillin in monotherapy for the treatment of non-meningeal pneumococcal infections within the first 48 hours in adults, an increase in mortality was not observed when the infection was caused by a strain with an MIC<2 μg/ml [9]. c) It is urgent to return to the use of reduced spectrum antibiotics. The increase in the use of broad-spectrum antibacterial agents has been accompanied by an increase in the rates of resistances of the microorganisms [10]. Moreover, the incidence of infection by *Clostridium difficile* is rising in parallel with an increase in the prescription of wide spectrum antibiotics [11]. d) No clinical study comparing amoxicillin and penicillin V in pneumonia in adults has been published. Amoxicillin is the first-choice option antibiotic for non-severe community-acquired pneumonia recommended by the Spanish Society of Family Medicine [12,13], and also endorsed by other scientific societies, such as the British Thoracic Society [14], and the European Respiratory Society/European Society for Clinical Microbiology and Infectious Diseases [15]. Although some clinical trials have compared amoxicillin with penicillin, these were performed in children and with parenteral doses [16-19].

## Methods

### Study hypothesis and objectives

The main hypothesis of this study is that the administration of high doses of penicillin V in patients with non-severe pneumonia attended in the community is not less effective than high doses of amoxicillin (currently recommended treatment) in patients under the age of 65 years without comorbidities. The main objective of this phase IV randomised, multicentre, clinical, double-blind, parallel, clinical trial is to evaluate the efficacy of phenoxymethylpenicillin (penicillin V) in the antibiotic treatment of non-severe pneumonia attended in the community compared with amoxicillin, considering the rate of clinical cure at 2 weeks. Secondary objectives are to assess the rate of radiological cure at 4 weeks in the patients treated with the two antibiotics, evaluate the rate of clinical cure at 4 weeks in both treatment groups, and evaluate the presence of adverse effects in the patients treated with the two antibiotics.

### Patient selection

Patients from 18 to 65 years of age without significant associated comorbidity attending the primary healthcare centres or emergency departments with signs and symptoms of lower respiratory tract infection and radiological confirmation of the diagnosis of pneumonia will be recruited in this clinical trial. Exclusion criteria will be subjects under 18 and over 65 years of age, severe impairment of signs (impairment of consciousness, respiratory rate > 30 breaths/minute, heart rate > 125 beats/minute, systolic blood pressure < 90 mm Hg, diastolic blood pressure < 60 mm Hg, temperature > 40°C, oxygen saturation < 92%), hypersensitivity to β-lactams, important alteration on chest X-ray, such as alveolar infiltrate in more than one lobe or bilateral, pleural effusion and/or pulmonary cavitation, problems to comply with treatment at home – sociopathy or psychiatric problems, drug and alcohol addiction, or within an inadequate family setting –, lack of tolerance to oral treatment, such as the presence of nausea and vomiting, gastrectomy, postsurgery and/or diarrhoea, significant comorbidity including bronchial asthma, renal failure, hepatic cirrhosis, heart failure, chronic obstructive pulmonary disease, ischaemic heart disease, stroke and/or type 1 diabetes mellitus, immunosuppression – chronic HIV infection, transplantation, neutropenic, or patients receiving immunosuppressive drugs or corticosteroids –, terminal disease, pregnancy or lactation, hospitalisation in the last month, consumption of antibiotics in the last two weeks, difficulty to attend the programmed visits or refusal to participate in the study.

### Randomisation

Patients will be randomly assigned to either penicillin V 1,600,000 units (two 800,000- unit pills) or amoxicillin 1,000 mg (two 500-mg pills) both taken thrice daily during 10 days. Subject numbers will be assigned sequentially as each subject enters the study. The subjects will be assigned a study drug through a randomisation schedule based on the randomisation plan. Since this is a multicentre study a block procedure will be undertaken for the assignment of each primary care centre participating in the study. Each container will include 66 pills (60 pills for the treatment plus 6 extra pills). The study drug, which will be prepared by the Pharmacy Unit of Hospital Universitari Son Espases (Palma de Mallorca, Spain) and will be labelled with the study number and a unique identification number.

Use of antithermic drugs or analgesics (acetaminophen, acetylsalicylic acid or ibuprofen), bronchodilators as well as any medication, except oral systemic antibiotics, that the patient is taking and which have been initiated prior to inclusion in the study will be allowed. Since this is a clinical study no statistically significant differences are to be expected in the concomitant treatment administered in the two treatment arms. In the case of clinical deterioration, the investigating physician will administer another antibiotic treatment in accordance with the clinical criteria.

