### Sample size

The objective of the study is to demonstrate that penicillin V is not inferior to amoxicillin. Considering a success rate of 85% for the group treated with amoxicillin [20,21] a total of 105 patients will be required in each treatment group (total of 210) to detect a non-inferiority margin of 15% at maximum between the two treatments with a minimum power of 80% considering an alpha error of 2.5% for a unilateral hypothesis and maximum possible losses of 15%.

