### Statistical analyses

The intention-to-treat (ITT) population will include all randomised patients receiving at least one dose of study drug and the per-protocol (PP) population will include patients receiving no systemic antimicrobial agents other than the study drug for at least three days in the case of clinical failure or ≥80% of study medication in the case of cure, with adequate assessment of compliance and absence of major protocol violations.

To evaluate the comparability of the groups the two groups will be analysed with variables expressed as means and standard deviations for the case of quantitative variables and with proportions in the case of qualitative variables. The variable of the principle result, clinical cure, will be expressed as percentages and the comparison of percentages in the two treatment groups will be analysed using the Chi-square test. Logistic regression will be performed for the analysis of the predictive factors of cure or not, with calculation of the odds ratio for each of the variables analysed and multiadjustment for each of the factors of the study with confidence intervals of 95%. Variables with a p<0.20 on bivariant analysis will be included in the analysis. A p value < 0.05 will be considered statistically significant.

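### Treatment is allocated in blocks by centre, but the primary Chi-square comparison leaves centre out: a mildly conservative mismatch that is cheap to correct

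*Protocol article*

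**What the plan says.** - **Allocation** (protocol article, Randomisation): "a block procedure will be undertaken for the assignment of each primary care centre participating in the study". Block size and number of centres are not given; elsewhere the article speaks only of several centres. Patient selection also admits patients from emergency departments, and the Randomisation section does not say to which block these belong.
- **Primary comparison** (Statistical analyses): clinical cure is expressed as percentages, and "the comparison of percentages in the two treatment groups will be analysed using the Chi-square test". No stratification or centre adjustment is mentioned.
- **Regression** (same section): a logistic model looks for predictors of cure, "with calculation of the odds ratio for each of the variables analysed and multiadjustment for each of the factors of the study with confidence intervals" at the 95% level. Entry is by screening: "Variables with a p<0.20 on bivariant analysis will be included in the analysis". No covariate is named, centre included.
- **Sample size**: the control rate is given as "Considering a success rate of 85% for the group treated with amoxicillin". From this the article derives 105 patients per arm, 210 overall. The margin is worded as "to detect a non-inferiority margin of 15% at maximum between the two treatments". Power is 80%, one-sided alpha 2.5% and losses 15%.

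**The concern.** Blocking within centre forces the arms to be nearly balanced in every centre. Differences in cure rate between centres then largely cancel out of the treatment comparison. An unstratified variance does not know this and still counts the between-centre variation as noise, so the standard error it reports is too large whenever centres differ.

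Differences between centres are plausible here. Under Outcome measures, cure rests on clinical signs such as a better cough, better general condition and fewer crackles, judged by physicians at several sites; the article describes radiologist review only for the X-ray findings. What is at stake is some efficiency: a stratified analysis may give a slightly tighter interval against the margin from the same patients.

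**Working it through.** **1. Reproduce the planned size.** Inputs from Sample size: 85% success, taken as equal in both arms (an assumption that reproduces the stated figure); margin 0.15; one-sided alpha 0.025 (z = 1.96); power 80% (z = 0.8416); losses 15%.

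- n per arm = 2 × 0.85 × 0.15 × (1.96 + 0.8416)² / 0.15² = 88.95, so 89.
- Inflated for losses: 89 / 0.85 = 104.7, so 105 per arm and 210 in total. This matches the article.

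The formula has no centre term, so 105 per arm already pays for an unstratified analysis.

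**2. Unstratified precision at 89 evaluable per arm.**

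- SE = sqrt(2 × 0.1275 / 89) = 0.0535, where 0.1275 = 0.85 × 0.15.
- 95% half-width = 1.96 × SE = 10.49 points.
- Power = Φ(0.15 / SE − 1.96) = 80.0%.

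**3. Effect of stratifying.** The between-centre SD of the cure rate is not in the article. It is assumed to be 0, 5 or 10 points. With arms balanced within centres:

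- variance ratio r = 1 − SD² / 0.1275
- stratified half-width = 10.49 × sqrt(r)
- excess width of the unstratified interval = 1/sqrt(r) − 1
- stratified power = Φ(0.15 / (SE × sqrt(r)) − 1.96)
- actual one-sided error of the unstratified analysis = Φ(−1.96 / sqrt(r))

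| Assumed SD | r | Stratified half-width | Excess width | Stratified power | Unstratified error |
|---|---|---|---|---|---|
| 0 | 1 | 10.49 | 0% | 80.0% | 2.5% |
| 5 points | 0.980 | 10.39 | 1.0% | 80.8% | 2.39% |
| 10 points | 0.922 | 10.07 | 4.2% | 83.1% | 2.06% |

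SDs of 5 and 10 points correspond to intraclass correlations (ICC = 1 − r) of about 0.02 and 0.08.

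**4. Check by simulation.** Assumptions: 180 patients, equal centres, blocks of 4 within centre, 85% mean cure; Wald interval against the Mantel-Haenszel risk difference with Sato variance. Mean half-widths in points, unstratified to stratified:

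| Centres | ICC 0 | ICC 0.01 | ICC 0.05 | ICC 0.10 |
|---|---|---|---|---|
| 6 | 10.34 to 10.35 | 10.32 to 10.29 | 10.25 to 10.05 | 10.20 to 9.77 |
| 15 | 10.35 to 10.35 | 10.33 to 10.28 | 10.30 to 10.05 | 10.30 to 9.80 |
| 30 | 10.36 to 10.53 | 10.35 to 10.48 | 10.34 to 10.27 | 10.32 to 9.98 |

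The direction and order of size agree with step 3. With 30 centres of six patients each and little between-centre variation, stratifying makes the interval slightly wider.

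**The case against.** The strongest case against runs as follows.

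- **No planned interval is too wide.** A reader might infer that the article's confidence interval for the primary result is wider than it should be. It plans none: its only stated intervals belong to odds ratios in the predictor model. The widths above concern the interval that would be needed to judge the 15-point margin. This stands.
- **No promised power is lost.** A reader might infer that the trial is underpowered because centre is left out. Step 1 shows otherwise: the unstratified analysis delivers the planned 80%, and stratifying adds to it. This stands.
- **Centre is not excluded from the regression.** The article lists no covariates at all, so this is silence. This stands.
- **Between-centre differences are not established.** Limitations and strengths relies on prior meetings with the investigators and physicians to make conduct homogeneous. Those meetings may not remove all variation, but the article supports only that cure rates may differ. That is why the range starts at zero.
- **This is detail for the full protocol or analysis plan.** That holds for weights and pooling rules, and an unseen plan may already stratify. It does not remove the point, because the article itself names the primary test and that test ignores the allocation it describes.
- **Sparse data.** About 178 × 0.15 = 27 failures are expected. Over an assumed 15 centres that is 27/15 = 1.8 each, so pooling could affect much of the sample. This is a real cost of the remedy.

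**Conclusion.** The point holds as a minor, conservative mismatch: allocation is blocked by centre and the named primary comparison does not take centre into account. The size rests wholly on an assumed between-centre SD of 0 to 10 points. Within that range, stratifying would gain at most about 3 points of power and 0.42 points (10.49 − 10.07) of half-width, and nothing if centres are alike. Leaving centre out creates no risk of a false claim of non-inferiority, because the one-sided error stays at or below 2.5%. It merits a low-priority recommendation. Two caveats apply: the Randomisation wording is loose, and the full protocol or analysis plan, not shown, may already provide a stratified analysis.

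**What to change.** Make the primary estimate the difference in cure rates, penicillin V minus amoxicillin, stratified by centre (for example with Mantel-Haenszel weights), with a two-sided 95% confidence interval whose lower limit is compared with -15 points. This would also give the article an interval tied to its margin, which a Chi-square test of equality does not provide.

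Before unblinding, fix:

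- how small centres, or centres with patients in only one arm, are pooled;
- to which stratum emergency-department recruits belong;
- that the unstratified interval is reported as a sensitivity analysis.

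If centre is to be left out, say why. The change needs no extra patients and only a little more analysis work. The downside is the pooling rule itself and, with many small centres and little variation between them, an interval that may be slightly wider than the unstratified one.

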### Blinding issues

We will perform a double-blind clinical study in which neither the physician nor the patient will know the treatment administered. The radiologists responsible for diagnosing pneumonia and confirming the radiological cure will be also blind to the clinical data and the treatment administered. The two medications will be presented as the same type of capsule. This will ensure that even on opening the container no one will know which medication has been given.

### Withdrawal

Each participant will have the right to withdraw from the study at any time. In addition, the investigator may discontinue a participant from the study at any time if the investigator considers it necessary for any reason including significant protocol deviation, significant non-compliance with the treatment regimen or study requirements (the patient will be required to return all the medication samples not taken to the investigator; if the remaining medication is not returned, compliance will be evaluated as insufficient), an adverse event which requires discontinuation of the study medication or results in inability to continue to comply with study procedures, disease progression which requires discontinuation of the study medication or results in inability to continue to comply with study procedures. In cases of clinical deterioration the medical investigator will implement another antibiotic treatment considering the clinical criteria, withdrawal of consent or loss to follow up.

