### Outcome measures

The variable of the main result will be clinical cure at 14 days, defined as absence of fever, resolution or improvement of cough, improvement of general wellbeing and normal respiratory auscultation or reduction of crackles indicating that no other antimicrobial treatment is necessary. Any clinical result other than the anterior will be considered as treatment failure. Variables of secondary results will be efficacy at day 30 after the initiation of antibiotic treatment, radiological resolution or improvement one month after the initiation of the treatment, complete clinical resolution at day 14 defined as the total resolution of acute symptoms and signs related to the infection, the presence of adverse events which may appear during the treatment, and compliance with treatment administered. The radiologists responsible for diagnosing pneumonia and confirming the radiological cure will be blind to the clinical data and the treatment administered.

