### Ascertainment of visits

On fulfilling the inclusion criteria the nature of the study will be explained to the patient and informed consent will be requested. All the eligible patients should have a chest X-ray (posteroanterior and lateral projection) demonstrating pneumonic infection. The study scheme and the visit program will be explained to the patient (Table 1). The patients will be randomised to one of the 2 treatment groups and the medication given. The first dose of the drug will be administered in the presence of the investigator. They will be dispensed the drugs for ten days.

**Table 1 T1:** Variables to be collected during the clinical trial

	**Visit 1**	**Visit 2**	**Visit 3**	**Visit 4**
	**Day 0**	**Day 3**	**Day 14**	**Day 30**
**Medical history and examination**	x	x	x	x
**Pulse oximeter determination**	x	x	x	x
**Chest X-ray**	x			x
**Informed consent form**	x			
**Randomisation**	x			
**Evaluation of clinical evolution**		x	x	x
**Assessment of adverse events**		x	x	x
**Review of compliance**		x	x	

At the first follow-up visit, scheduled at day 3, a worsening of the clinical situation of the patient will be evaluated to determine whether a change in the antibiotic treatment is necessary. Likewise, compliance and possible secondary effects of the treatment will be evaluated. At the second follow-up visit, at day 14, the clinical evolution of the signs and symptoms will be evaluated and the need to change the antibiotic treatment in the case of worsening in the clinical manifestations will be determined. Likewise, compliance and possible secondary effects of the treatment will be evaluated. The last follow-up visit, scheduled at day 30, the clinical outcome of the signs and symptoms of the pneumonia will be evaluated and a new chest X-ray will be performed (posteroanterior and lateral projection) to confirm radiological resolution of the pneumonia. The medication will be discontinued in the case of clinical failure in follow-up visits 2 and 3 or in the case of significant adverse events.

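### The Withdrawal section lets an investigator take a patient out of the study solely because an adverse event stopped the drug, so the scheduled day-14 and day-30 assessments may be missed

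*Protocol article*

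**What the plan says.** Two sections of the protocol article deal with a patient whose adverse event stops the study drug.

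- **Withdrawal.** The opening power is broad: "the investigator may discontinue a participant from the study at any time if the investigator considers it necessary for any reason". Among the reasons then listed is "an adverse event which requires discontinuation of the study medication or results in inability to continue to comply with study procedures". Disease progression is listed with the same two limbs, and significant non-compliance with treatment is also a reason.
- **Ascertainment of visits.** The consequence here concerns the drug alone: "The medication will be discontinued in the case of clinical failure in follow-up visits 2 and 3 or in the case of significant adverse events". Leaving the study is not mentioned. In Table 1 the row "Assessment of adverse events" is marked at days 3, 14 and 30, and no patient group is excepted.

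Three other statements bear on what could be lost. A secondary objective is to "evaluate the presence of adverse effects in the patients treated with the two antibiotics". Under Outcome measures, the safety variable is "the presence of adverse events which may appear during the treatment". The same section fixes the primary endpoint: "The variable of the main result will be clinical cure at 14 days".

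**The concern.** Stopping a drug and leaving a trial are different acts. The first need not affect data collection; the second normally ends it. The Withdrawal section makes the first a sufficient reason for the second, while the visit section treats the same event as a matter of medication only. Two sites could follow the text faithfully and handle identical patients differently.

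At stake is follow-up in the patients who tolerated their capsules worst. If such a patient is taken out of the study, the outcome and duration of the event, and anything that develops afterwards, may not be recorded. If the two regimens differ in tolerability, this loss would differ between arms. The comparison of adverse effects is a stated objective, and a safety board is planned because the penicillin V dose is high and seldom used locally. The day-14 visit also carries the primary outcome, so removal before then would cost that assessment too.

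**Working it through.** The point turns mainly on wording, so the check sets the sections side by side. It then looks at how much room the sample size leaves for avoidable losses.

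**1. Is stopping the drug sufficient for removal?** The listed reason has two limbs joined by *or*: the event requires the medication to be stopped, or it leaves the patient unable to comply with study procedures. Since inability is a separate limb, the first applies to a patient who could still attend. So stopping the drug is sufficient.

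**2. Is removal obligatory?** No. The power is introduced by *may* and depends on the investigator finding it necessary. By contrast, the drug stop in Ascertainment of visits is introduced by *will*.

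**3. Does the article say what happens to visits afterwards?** It does not say that visits continue once the drug is stopped, nor that they end. Table 1 simply lists them.

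**4. What would a removed patient lose?** Treatment lasts 10 days, and adverse events are assessed at days 3, 14 and 30.

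- For a patient who stops after the day-3 visit and is removed, day 3 is the last scheduled assessment completed.
- The event that caused the stop is already known.
- Not systematically collected would be its resolution, later events, and any other event that began on treatment but had not yet been reported.
- The day-14 cure assessment is lost as well. The patient nevertheless stays in the intention-to-treat population, which takes in every randomised patient with at least one dose (Statistical analyses).

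**5. How much room is there for losses?** Inputs from Sample size: 85% success on amoxicillin, margin 15 points, one-sided alpha 2.5%, power 80%, losses 15%. Assumption: 85% on penicillin V too, which the article does not state.

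- Evaluable per group: n = (1.96 + 0.8416)² × 2 × 0.85 × 0.15 / 0.15² = 88.95, rounded up to 89.
- With losses: 89 / 0.85 = 104.7, rounded up to 105 per group, 210 in total. The plan's figure is reproduced.
- Power with 105 randomised per group and a fraction d lost: Φ(0.15 / √(2 × 0.85 × 0.15 / m) − 1.96), where m = 105 × (1 − d).

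| Losses | m per group | Power |
|---|---|---|
| 0% | 105 | 86.1% |
| 10% | 94.5 | 82.3% |
| 15% | 89.2 | 80.1% |
| 20% | 84.0 | 77.7% |

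The stated power is just met at the planned 15% losses. This is a scale check only and disputes no figure in the plan.

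**6. How many patients are affected?** That number is the share who stop for an adverse event, times the share of those whom investigators then remove, times 210. The article gives neither share, so the product cannot be computed.

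**The case against.** The strongest reply is that the article contains no contradiction. A mandatory drug stop and a discretionary study withdrawal can coexist, and an investigator who stops the drug and keeps the patient in follow-up complies with both sections. The safety variable is limited to events during treatment, so for a patient who stops early the comparison as defined loses little. The text is also a condensed article: an early-termination visit or follow-up of events to resolution may be set out in the full protocol, and the trial commits to good clinical practice guidelines.

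Much of this stands. A reader might infer that patients who stop for an adverse event lose their later visits by rule; the text gives a permission, not a rule. A reader might also infer that the adverse-effect comparison is seriously damaged, or that the safety board would miss the events; nothing suggests that an event leading to withdrawal would go unreported.

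It is also tempting to put a number on the loss. If 5% of patients stopped for an adverse event (range 2% to 10%), 0.05 × 210 = 10.5 patients (4.2 to 21) would be affected, against 0.15 × 210 = 31.5 allowed losses. But those percentages are not in the documents, and the sum also assumes that every such patient is removed.

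What does not fall away is the stated ground for removal. This is not an omission that an article may leave to a fuller document: the text itself makes a drug stop a sufficient reason to leave the study, and it does not limit that by the patient's ability to attend.

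**Conclusion.** The concern holds as a defect of wording with a real but unquantified consequence. The article permits removal from the study solely because an adverse event stopped the medication, beside a section that stops only the medication and a schedule that makes no exception. Where investigators use the power, patients may miss the day-14 and day-30 assessments, chiefly at the cost of event resolution and later events. Such losses would be avoidable and would concern patients whose outcomes are informative. The same reasoning covers the parallel wording on disease progression.

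The conclusion rests on reading *or* as separating two sufficient reasons, and on removal from the study ordinarily ending its visits, which the article neither confirms nor denies. It does not rest on any assumed rate of discontinuation. The sponsor should act on it because the remedy is cheap and the sample size has little room beyond the losses already allowed.

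**What to change.** Reconcile Withdrawal with Ascertainment of visits:

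- Treat discontinuation of study medication and withdrawal from the study as two separate acts, each with its own reasons.
- State that patients who stop the medication remain in follow-up for the scheduled day-14 and day-30 visits unless they withdraw consent, are lost to follow-up or cannot continue study procedures.

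The third exception matters. Restricting withdrawal to consent and loss to follow-up alone would go further than the problem requires. The rules on when to stop the medication stay as the sponsor decides. The change is one of protocol wording and the downside is minor, because Table 1 already schedules both visits.
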